**How the planned methods achieve the aim or research questions**

**Primary outcomes:**

Participants will have been diagnosed with PDMM according to the criteria specified in the International Classification of Diseases criteria (ICD-10-I63; Code: 902) [10]. Moreover, VAS scores will be recorded before and after treatment (i.e., during the follow-up period). We adopted a methodology based on the VAS card created by the Pain Society of the Chinese Medical Association, ranging from “no pain” (at 0 cm on the left side of the scale card) to “the most severe pain” (at 10 cm on the right side of the scale card). The distance from the starting point of the scale to the patient evaluation measurement is recorded in cm. The VAS score is measured by the patient placing the cursor at the area best representing their subjective level of pain at the time of evaluation. The score is recorded according to the position of the cursor

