**Secondary outcomes:**

Pain level on this scale is indicated by 11 numbers ranging from 0 to 10 (0 = painless, 10 = the most painful). The degree classification standard was scored as follows: 0 = painless, 1 to 3 = mild pain, 4 to 6 = moderate pain, 7 to 10 = severe pain. The participants will be scored according to their individual pain sensations. This method is easily understood by patients and can be either dictated or written. The CMSS is a total frequency score indicating an average severity evaluation of menstrual dysmenorrhea and includes information on specific symptoms of menstrual dysmenorrhea. Moreover, the traditional Chinese medicine symptom Score is formulated to score the evaluation of Chinese medicine symptoms according to the Guiding Principles for Clinical Research published by the Chinese Medical Science and Technology Press. The Self-Rating Anxiety Scale, Self-Rating Depression Scale, and 36-Item Short Form Survey are scales used to evaluate participants' mood and quality of life during treatment and follow-up. A metabolomics test on blood and urine samples is to be used to evaluate metabolic product changes occurring after the treatment of PDMM with EA and to provide findings informing the evidence base about putative mechanisms associated with metabolic pathways affected by EA.

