**Statistical analysis:**

Descriptive statistics

We will perform statistical analyses using SPSS statistical software (version 26.0, IBM Corp., Armonk, NY, USA). A mixed-effect model will be used to compare change values before and after treatment for continuous variables. This analysis model divides the baseline scores as study covariates, accounting for grouping and central effects. Based on this model and differences before and after treatment, we will calculate the least squares mean of the two groups and the associated 95% credible interval of the difference between the two groups. Fisher's exact parametric method and nonparametric Kruskal Wallis tests will be used to evaluate dichotomous variables. Report exact p-values for all values greater than or equal to 0.001.A two-sided P-value of < 0.05 is considered the threshold for statistical significance.

Metabolomics analysis

We will perform first signal denoising, baseline and phase correction for all spec graphs, piecewise data integration, row and column normalization, and scaling normalization to conduct the metabolomics analysis. All data are to be processed using MestReNova software (Mestrelab Research, Santiago de Compostela, Spain). Pattern recognition analysis includes adopting the principal component analysis method of unsupervised mode recognition as well as a classification analysis (SIMCA), a partial least squares method, and a neural network method. All of these procedures will be conducted using SIMCA-P software (version 14. 0, Umetrics AB, Umea, Sweden). Pearson correlation analysis will be used to analyze characteristic hematuria metabolites as well as to determine the metabolites specific to PDMM and their associated metabolic pathways.

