**Statistical analysis**

For the primary outcome, rates of recruitment (numbers consented/eligible), completion (undertaken baseline and follow-up tests), adherence (participant completed sessions/number of sessions), and adverse events (number and number per participant hour) will be calculated. Secondary outcome will be assessed following intention-to-treat principles. Repeated measures ANOVA will be conducted to assess changes in secondary outcomes throughout the study. This model allows inclusion of missing data in an intention-to-treat analysis without imputations (e.g. last-observation-carried-forward). If necessary, analysis will be adjusted for baseline levels and potential confounding factors. Normality assumptions will be assessed using the Shapiro-Wilk test. Statistical significance will be set at an alpha level of 0.05. Corrections will be applied to all analysed outcomes to account for multiple comparisons.

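### The two analysis sections are inconsistent on multiplicity, and the second, read literally, would correct the single primary VAS comparison for the secondary scales

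*Protocol*

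**What the plan says.** The first Statistical analysis section, which follows Secondary outcomes, gives the model for continuous outcomes: "A mixed-effect model will be used to compare change values before and after treatment for continuous variables". Its significance rule is: "A two-sided P-value of < 0.05 is considered the threshold for statistical significance". It does not mention multiple testing.

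The second Statistical analysis section, which precedes Risk, gives its own threshold, "Statistical significance will be set at an alpha level of 0.05", and then adds "Corrections will be applied to all analysed outcomes to account for multiple comparisons". It names no method, no family of tests and no exempt outcome. It analyses secondary outcomes by repeated measures ANOVA.

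The sections also differ on what is primary. The Primary outcomes section is about the pain scale ("VAS scores will be recorded before and after treatment"), and inclusion criterion 8 refers to VAS as the primary endpoint. The second analysis section begins "For the primary outcome, rates of recruitment (numbers consented/eligible), completion (undertaken baseline and follow-up tests), adherence", continues with adverse events, and does not mention VAS.

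The Secondary outcomes section lists a 0–10 numeric pain score, the CMSS, a traditional Chinese medicine symptom score and three mood and quality-of-life instruments ("The Self-Rating Anxiety Scale, Self-Rating Depression Scale, and 36-Item Short Form Survey are scales used to evaluate participants' mood and quality of life"). That is six scales, plus metabolomics.

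**The concern.** A single pre-specified primary comparison needs no adjustment for secondary outcomes, because its type I error is already held at the nominal level. The second section makes no such exception. VAS is an outcome that will be analysed, so the literal rule covers it.

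Two things are at stake. If the correction is spread across outcomes, the primary test loses power and gains nothing. And the protocol does not settle whether a given VAS result is positive: a reader of the first section compares P with 0.05, while a reader of the second compares it with something stricter. Both sections are current text, and neither refers to the other or takes precedence.

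The secondary scales raise the converse question. If only the first section is followed and significance is claimed on each of six scales, nothing in it limits the chance of a false positive among them.

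**Working it through.** **The plan's own figure.** The synopsis gives 168 per group and 336 in total, and 168 × 2 = 336 agrees. The 168 cannot be reproduced, because the protocol states no effect size, standard deviation, alpha, power or dropout. Everything on power below is therefore illustration.

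**The sections side by side.**

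| | First section | Second section |
|---|---|---|
| Threshold | two-sided 0.05 | 0.05, sidedness not stated |
| Correction | not mentioned | all analysed outcomes, no method |
| Primary outcome | not named (VAS in the Primary outcomes section) | feasibility and adverse-event rates, no test named |
| Model | mixed-effect model | repeated measures ANOVA (secondary outcomes) |

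**Does the choice of section change a conclusion?** Take a VAS P-value of 0.02. Against 0.05 it is significant. Under Bonferroni over two outcomes the limit is 0.05/2 = 0.025 and it still passes. Over three the limit is 0.05/3 = 0.0167 and it fails. The protocol has VAS plus six scales, so under Bonferroni across outcomes it would fail.

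**Power cost to the primary.** Assumptions: 168 per arm analysed, no dropout, two-sided normal approximation, and a design power of either 80% or 90% at 0.05.

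- Implied standardised difference: d = (z for alpha + z for power) × √(2/168). For 80%: (1.960 + 0.842) × 0.1091 = 0.306. For 90%: (1.960 + 1.282) × 0.1091 = 0.354.
- Bonferroni over seven outcomes (VAS and six scales): alpha = 0.05/7 = 0.0071, critical value 2.690.
- Power = Φ(d × √(168/2) − 2.690). For the 80% case: Φ(2.802 − 2.690) = Φ(0.11) = 54%. For the 90% case: Φ(3.242 − 2.690) = Φ(0.55) = 71%.
- Restoring the assumed power at that alpha would need about 267 or 253 per arm instead of 168.

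The result depends on the size of the family. Over two outcomes the figures are 71% and 84%. Over eight, counting metabolomics as one test, they are 53% and 69%. Seven is used here because the first section describes metabolomics as pattern recognition and correlation analysis, not as one hypothesis test.

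**Error rate among the secondary scales without correction.** For k independent tests at 0.05 with no true effect, the chance of at least one false positive is 1 − 0.95^k. With k = 6, 1 − 0.95^6 = 0.265. Pain, mood and quality-of-life scores are likely to be positively correlated, so the true figure would be lower.

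**The case against.** The strongest reply is that the sections do not contradict each other. Both state 0.05, and the first is silent on correction; it does not rule one out. Applying 0.05 to adjusted P-values would satisfy both. This stands in part. A reader might infer that the sections lay down opposite rules, or that the first prescribes an uncorrected 0.05 for every outcome, but the text supports neither. It supports an inconsistency: one section promises a correction that the other does not mention.

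Second, the second section never says that VAS is corrected. It does not name VAS, and its own primary outcome is a set of rates that are only calculated. This also stands. Correction of VAS follows only from reading the sentence about all outcomes together with the Primary outcomes section and inclusion criterion 8. But if the primary outcome were put right and the last sentence kept, VAS would fall squarely under the correction.

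Third, the sentence closes a paragraph on repeated measures, so it could mean comparisons across time points within an outcome. That reading is possible. The wording is about outcomes, though, and the protocol does nothing to choose between the readings.

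Fourth, the method and the family belong in a statistical analysis plan, which may exist. That is fair for the choice between Holm and Bonferroni. The scope, however, is fixed in the protocol: a later plan that tested VAS uncorrected would depart from its literal wording.

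Finally, the power and error figures are not the trial's own. They rest on an assumed design power, Bonferroni and independent tests; Holm would cost less power.

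**Conclusion.** The point holds as an inconsistency that should be resolved before analysis. The protocol promises a correction in one place and omits it in another. Taken literally, the promise covers a single primary comparison that needs none. Its cause is wider: the second analysis section does not match the outcome sections on the primary endpoint or the first analysis section on the model, and the multiplicity sentence is one part of that mismatch.

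The illustrative cost is a fall from an assumed 80% to about 54%, or from 90% to about 71%, with Bonferroni over seven outcomes. Without any correction, the six secondary scales would carry at most about 26% family-wise error if independent or positively correlated. These figures show why the wording matters. A reader might infer from them that the trial is underpowered, but the protocol gives no design inputs from which to judge that.

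A reader might also infer that the sponsor must choose between losing power on the primary and leaving the secondary outcomes unprotected. That does not follow: an uncorrected primary with a separate rule for the secondary outcomes avoids both.

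**What to change.** Replace the last sentence of the second Statistical analysis section as a whole. Deleting only the words that extend it to every outcome would leave a correction with no scope and still no exemption for VAS. Align the first section so that one rule applies:

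- The primary VAS comparison of electroacupuncture with sham, at the protocol's primary time point, is tested alone at two-sided 0.05 without correction.
- The six secondary scales are either tested under one named correction, for example Holm, or reported with estimates and intervals and no confirmatory claims. Either choice would do.

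In the same edit, reconcile the primary outcome in the second section with the Primary outcomes section.

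The cost is wording, with no change to sample size or data collection. The downside is that some secondary results may lose the label of significance.

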**Risk**

**Physical Risks**

All adverse events shall be recorded in detail and handled and tracked until properly resolved or stable, and serious adverse events shall be reported to the ethics committee and competent authorities as required according to institutional regulations and relevant laws. The principal investigator shall conduct a cumulative review of all adverse events and hold an investigator meeting if necessary to reassess the risks and benefits of the study in light of the new information arising during the course of the study. Once an adverse event is identified, this event shall be followed-up until it is resolved or until the adverse event is determined to be permanent.

Moreover, researchers must assess changes in the severity of the adverse events occurring during the course of the study, suspicious reactions to the study treatment, and the need for intervention at each visit (including recommending increased study visit frequency if needed). All adverse events must be recorded on the adverse events page of the CRF. Adverse events must be recorded with regard to time, severity, and duration parameters, as well as with relevant information on measures and outcomes. Adverse events must be carefully and accurately recorded during the trial. Adverse events are to be divided into acupuncture-related and non-acupuncture-related events according to their potential reactions with the acupuncture treatment process.
